## Discussion

The RTP study is one response to recommendations to examine the impact of P4P on improving the quality of care [87], and it represents the largest known randomized experiment to date to evaluate the impact of P4P methods at the staff level within the substance abuse treatment field. The study design was based on taking into consideration key P4P design elements as described by Rosenthal and Dudley [88], who have identified five key design elements of P4P programs. The following section briefly describes each of these elements and how they have been addressed in this study.

### 1. Individual versus group

The first element relates to whether the P4P initiative targets individuals or the organization. According to Rosenthal and Dudley [89], 14% of programs focused on individuals alone, 25% focused on both individuals and groups, and 61% focused on groups alone. However, consistent with their recommendation to provide incentives to the group or individual that is most responsible for the targeted behavior, therapists were selected as part of the RTP study given they are the ones who must ultimately implement the treatment with clients.

### 2. Paying the right amount

In order for an incentive to be effective, it must be commensurate with the costs in time and effort associated with achieving the targeted behavior. This is similar to the concept of financial salience being measured as part of the RTP study. Importantly, given the paucity of studies within the field of alcohol and drug treatment that have used P4P methods, determining appropriate incentive amounts was perhaps the most difficult aspect of designing the study. That is, incentive amounts selected had to simultaneously be large enough to significantly improve therapist performance, and small enough to be considered within a practical range for community-based treatment providers to implement.

Calculations suggested that full-time therapists in the P4P condition would earn on average an amount between $1,404 and $2,412 per 12-month period, which equated to approximately 4% to 7% of an average annual therapist salary of $35,000. While we believe these amounts are within a range that is practical for community-based treatment providers, the study will help us learn whether or not these incentives are large enough to impact performance.

### 3. Selecting high-impact performance measures

The third element relates to linking the incentives to performance measures that are meaningful and/or based upon sound scientific evidence and is similar to the concept of clinical relevance being measured as part of the RTP study. While research to date has provided only limited empirical support for the relationship between competency and outcomes, we believe this targeted behavior has considerable intuitive appeal and therefore will be perceived by therapists as being clinically relevant. Similarly, we believe therapists will find Target A-CRA to be a clinically meaningful performance measure, especially given the recent empirical evidence indicating that exposure to A-CRA procedures mediates the relationship between treatment retention and outcome [65].

### 4. Making payment reward all high-quality care

The fourth element relates to rewarding all who meet or exceed some threshold level of 'high quality care' as opposed to rewarding only the top performers (*e.g.*, top 10%)--the latter of which tends to create competition between providers and consequently decrease collaboration and sharing of ideas. Consistent with this recommendation, both Target A-CRA and Demonstration of Monthly A-CRA Competence represent threshold levels of high quality care, and achievement of one or both by one therapist does not reduce the opportunity for another therapist to also achieve the incentive.

### 5. Prioritizing quality improvement for underserved populations

The fifth element relates to reducing disparities in health and healthcare quality by offering relatively larger incentives for providing high-quality care to disadvantaged populations. Although the incentive amounts offered as part of the RTP did not differ for underserved populations, it may be possible to examine if there were differential rates of achievement of the targeted behaviors by race/ethnicity and/or gender.

### Study strengths and weaknesses

In addition to the use of random assignment, the RTP study has several other strengths. For example, a unique strength of the RTP study is the level of standardization in regard to the funding and training provided to the 29 participating agencies and their therapists. Specifically, because CSAT's approximately $30 million dollar AAFT initiative provided each of its grantees with close to $300,000 per year (for three years) as well as a comprehensive training and technical assistance package (via a separate training contract), the AAFT initiative provided an ideal opportunity to focus on examining the effectiveness and CE of P4P to improve EBT implementation and subsequent treatment outcomes for clients. Other strengths of the study include its: use of a theoretically-based conceptual framework; multi-site design; relatively large sample size; independent verification of therapist achievement of targeted behaviors; longitudinal assessment of therapist attitudes and client outcomes; inclusion of CE analyses; and hypothesis-driven multilevel analytic plan. Like all studies, however, the RTP study also has some limitations that must be acknowledged. First, although larger than any other known P4P experiment conducted to date, a greater number of sites and therapists would provide more statistical power and better generalizability. A second limitation of the study is that randomization was conducted by grantee rather than by therapist. However, as discussed previously, we believe the potential disadvantages associated with randomizing therapists within site (*e.g.*, compensatory rivalry, resentful demoralization) outweighed its advantages. Finally, because the targets being reinforced as part of this study are specific to the delivery of A-CRA procedures, the findings from this study may not generalize to other interventions and/or healthcare or behavioral health settings.

### Next steps

Although the recruitment and randomization of AAFT grantees has been completed, it is possible that additional therapists will be recruited as AAFT grantees hire new therapists. Indeed, this aspect of the RTP study is interesting in that in direct contrast to most studies, where attrition decreases statistical power, attrition actually has the potential to increase statistical power, given that therapists are typically replaced. Additionally, our research team continues to monitor therapist achievement of both Target A-CRA and Monthly A-CRA Competence and to administer both the therapist surveys and the TCAT. Given the study has just ended its first of three years, it will be some time before we are able to report on the impact of the incentives on therapist achievement of the targeted behaviors and on subsequent client outcomes. However, we plan to begin testing other parts of our conceptual framework. For example, we plan to examine the extent to which therapists' attitudes toward the incentives and TPB constructs explain variance in their intentions to achieve these behaviors. Given the increasing need to not only understand what interventions work, but how they work [89,90], research to understand the mechanisms through which reinforcing therapist performance via monetary incentives work is a critically important step.

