**Design:**

Using a cluster randomized design, substance abuse treatment therapists from across 29 sites were assigned by site to either an implementation as usual (IAU) or pay-for-performance (P4P) condition.

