### Overview of RTP study design

This RTP experiment and the rest of this article focus on improving the implementation of A-CRA/ACC. As part of the comprehensive A-CRA/ACC training model received by both RTP groups, participants: read the A-CRA manual and pass a knowledge test prior to training; attending a 3.5-day training workshop; participate in bi-weekly telephone coaching calls with treatment model experts; receive quantitative and qualitative feedback on actual session performance throughout the certification process; receive feedback on actual session performance as part of randomly selected post-certification fidelity checks; and provide documentation of treatment implementation via therapist reports of procedures delivered during each treatment session as well as corresponding digital session recordings (DSRs) of the session. Thus, with 34 grantees across 15 states, the AAFT project represents one of the field's largest dissemination and implementation initiatives of an adolescent substance abuse treatment intervention to date. More importantly, the standardized level of funding and training being delivered to the 34 CSAT grantees provides an ideal setting in which to examine methods to improve implementation.

RTP is a cluster randomized experiment examining the effectiveness and CE of providing monetary incentives to therapists as a method to improve treatment implementation and subsequent outcomes for adolescents and their caregivers. It builds upon prior work by Garner and colleagues [65] that has shown exposure to A-CRA procedures significantly mediates the relationship between treatment retention and outcomes, and empirically identified a threshold level of A-CRA exposure significantly related to positive post-treatment outcomes (*i.e.*, being in recovery). Additionally, it builds upon research that has examined the relationship between therapist competency and treatment outcome for clients [36,69,70]. ACRA/ACC sites and therapists within site were recruited to participate in the study, and those who agreed were randomly assigned to either implementation as usual (IAU) or P4P. Participation was voluntary and the study is conducted under the supervision of Chestnut Health Systems Institutional Review Board (IRB). Below are further descriptions of the intervention, procedures, measures, and analytic plans.

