### Staff recruitment

Recruitment of therapist participants for the study began one month after site recruitment. In order to be eligible to participate in the study, therapists had to work at one of the participating AAFT grantee sites and be delivering A-CRA or ACC to adolescents. Study packets containing a cover letter, informed consent, staff survey, and a W-9 tax form were mailed to 92 eligible therapists. Of these, 82 (89%) agreed to participate.

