Although urn randomization was conducted at the site level, it resulted in a balanced distribution of therapists into the two study conditions (See Table 1). Of the 82 therapists used to randomize sites most were female (74.4%) and Caucasian (56.1%). They had an average age of 37 years (SD = 11.6). In terms of their education and work experience, most had either a Masters (52.4%) or a Bachelor's (41.5%) degree, with an average of 4.3 years of substance abuse counseling experience. Seven percent reported personally being in recovery for alcohol or other drugs. Based on therapist self-report, the average achievement of Target A-CRA implementation prior to the experiment was 19.2%, and the average session recording rate of fidelity was 41.0%. Based on three-month post-intake follow-up data prior to the experiment, the average percentage of therapists' adolescent clients in recovery was 45.9%. Notification to sites and individual participants about the official commencement of the study and their assignment to either the IAU or P4P conditions were sent via email on 16 January 2009 for the AAFT-1 and on 13 February 2009 for AAFT-2.

**Table 1 T1:** Baseline characteristics of therapists at randomization

	P4P (n = 42)	IAU (n = 40)	Overall (N = 82)
	% or M (SD)	% or M (SD)	% or M (SD)
**Age**	36.7 (11.3)	36.7 (12.2)	36.7 (11.6)
			

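### Replacing departed therapists is presented only as a possible power gain, although replacements consent after their site's arm is known and add no randomised sites

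*Protocol article*

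**What the plan says.** The Design paragraph of the abstract states that "substance abuse treatment therapists from across 29 sites were assigned by site" to one of two conditions. Staff recruitment reports that 92 eligible therapists were approached: "Of these, 82 (89%) agreed to participate". The Randomization section says that these 82 were the therapists used to randomise the sites, and that notices of assignment "were sent via email on 16 January 2009 for the AAFT-1 and on 13 February 2009 for AAFT-2".

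Next steps says that grantee randomisation is complete and adds: "it is possible that additional therapists will be recruited as AAFT grantees hire new therapists". It then contrasts the study with most others, on the ground that "attrition actually has the potential to increase statistical power, given that therapists are typically replaced".

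Study strengths and weaknesses lists too few sites and therapists as a first limitation, and continues: "A second limitation of the study is that randomization was conducted by grantee rather than by therapist". Neither section mentions that later recruits know their arm, or that turnover may differ between arms.

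**The concern.** Recruiting participants after the cluster's allocation is known is a recognised route to bias in cluster trials. Here the incentive is the intervention. A new hire at a P4P site is asked to consent with $200 and $50 bonuses on offer. A new hire at an IAU site has none. The article expects bonuses worth about 4-7% of an average salary, so P4P could plausibly affect who leaves, who is hired and who agrees to take part.

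H1.1 (Target A-CRA) and H1.2 (monthly competence) are most exposed, because both are measured through participating therapists. If later hires are pooled with the original 82, the comparison depends partly on events that follow allocation. The Next steps section mentions only the favourable side, the possible gain in power.

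**Working it through.** **No power figure to reproduce.** The article gives no power, effect size, intraclass correlation or turnover rate. Its recruitment count checks: 82/92 = 89%.

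**Order of events.** The 82 therapists consented before their sites were notified. Later hires join after grantee randomisation is complete, so they consent after notification. Participation is voluntary, and only P4P therapists can earn bonuses.

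**Inputs for precision**
- From the article: 29 sites; k = 82/29 = 2.83 therapist positions per site; 36-month grants recruited in months 27 and 15, leaving M = 36 - 27 = 9 or 36 - 15 = 21 months.
- Assumed: site share of variance s = 0.05-0.20; therapist share t = 0.10-0.20; remainder e = 1 - s - t.

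**Main calculation: a replacement takes over part of the same position.** Variance of a site mean:
- no turnover: s + (t + e/M)/k
- every position replaced once: s + (t + 2e/M)/(2k), so only the therapist term is halved
- as above with a three-month vacancy: s + (t/2 + e/(M - 3))/k

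Example with s = 0.05, t = 0.20, M = 21 (e = 0.75): 0.05 + (0.20 + 0.0357)/2.83 = 0.1334 without turnover and 0.05 + (0.10 + 0.0357)/2.83 = 0.0980 with replacement, a fall of 26.5%.

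Fall in site-mean variance, full replacement / with three-month vacancy:

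| s | t | M = 9 | M = 21 |
|---|---|---|---|
| 0.05 | 0.10 | 14.9% / 0.8% | 17.7% / 15.3% |
| 0.05 | 0.20 | 23.5% / 13.7% | 26.5% / 24.9% |
| 0.10 | 0.10 | 10.6% / 1.2% | 11.9% / 10.4% |
| 0.10 | 0.20 | 17.8% / 10.9% | 19.4% / 18.3% |
| 0.20 | 0.10 | 6.7% / 1.5% | 7.2% / 6.4% |
| 0.20 | 0.20 | 12.0% / 8.0% | 12.6% / 12.0% |

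The range is about 7-27%, or about 1-25% with vacancies. On the standard-error scale, full replacement gives about 3-14%. However many therapists pass through, the variance cannot fall below s.

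**More generous calculation: each replacement counts as a whole extra therapist.** With site intraclass correlation rho and m therapists per site, the variance is rho + (1 - rho)/m. Take 50% more therapists (m from 2.83 to 4.24) and an effect that had 80% power at the start (two-sided 0.05, 27 degrees of freedom):
- rho = 0.05: variance 0.386 to 0.274; standard error down 16%; power 91%
- rho = 0.50: variance 0.677 to 0.618; standard error down 4%; power 83%

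**Selection.** If a share q of the analysed therapists joined late, and selection alone makes late joiners differ by d points between arms, the estimate moves by q × d. With 50% more therapists, q = 0.5/1.5 = 0.33. For assumed d of 5, 10 and 15 points the shift is 1.7, 3.3 and 5.0 points. Adding therapists at the same q does not reduce it.

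**The case against.** The power sentence is hedged, and in direction it is right: the calculation gives a gain in every scenario examined. A reader might infer that the sentence is false or that the gain is negligible. Neither is supported. Without an intraclass correlation or a turnover rate, a fall of about a quarter in variance cannot be excluded.

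A reader might also infer that the comparison is already biased. The documents do not show this. Further recruitment is described only as possible, and no number of late recruits, late consent rate or turnover by arm is given. Nor does the article say that late hires enter the main analysis. That rule may properly stand in a fuller document, and its absence here is not the point.

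The analytic plan places sites at the top level of all three models, so replacements would be treated as clustered within sites. The first listed limitation already concedes limited power.

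Finally, it is tempting to conclude that the 82 must be the sole primary set. That goes too far. Leavers stop contributing months and admissions, so that set is itself open to exit that differs by arm. If the question is what offering P4P at a site does, including staff hired there is a legitimate choice.

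What survives is narrower. The article presents replacement as an advantage without the accompanying risk, although it takes care over the same issue for adolescents: Target A-CRA analyses are limited to those admitted after randomisation, so that improvement can be attributed to the incentives.

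**Conclusion.** The concern holds in a limited form. Replacements consent with their arm known and do not increase the 29 randomised sites. The precision gain is bounded by the between-site variance and uncertain in size. The figures of about 7-27% and 1-25% rest on assumed variance shares, on remaining follow-up read from the grant months, and on every position being replaced once. The selection risk for H1.1 and H1.2 is plausible because bonuses exist in one arm only, but its size is unknown. The shifts of 1.7-5.0 points are illustrations, not estimates. The power remark is incomplete rather than wrong. This is a cheap improvement, not a flaw that invalidates the trial.

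**What to change.** - Pre-specify an analysis of H1.1 and H1.2 in the 82 therapists who consented before notification, with the adolescents they admit after randomisation. Set it beside the analysis that includes later hires, and read any divergence as possible selection.
- Report by arm the number of therapists who leave, the number of new hires approached and the number who consent.
- For H1.3, analyse all adolescents admitted at the 29 sites after randomisation. The de-identified GAIN data come through agreements signed by each site, so this set need not depend on therapist consent.
- Qualify the power sentence: precision is limited by 29 randomised sites, replacements are not independent randomised units, and their consent follows disclosure of the arm.

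The cost is a little more analysis and simple tracking of exits and approaches. The estimate in the 82 will be less precise and remains open to arm-dependent exit, which is why both analyses should be shown. The article reports that only the first of three study years had ended, so at the time of writing the rule could still be set before outcomes were analysed.
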